#### Direct mail guidance strategy

The direct mail guidance strategy consists of sending direct mail to the construction companies and workers in a paint pot where workers are informed about prevention of falling hazards with rolling scaffolds, ladders and stairs. The paint pot contains a poster with URLs for the Internet approach (http://www.schilderenophoogte.nl) to four types of information and instruction materials: brochures and poster, checklists (instructions for safe installation and use of equipment), video and toolbox (to inform and instruct workers during toolbox meeting). A falling paint pot is illustrated on the poster and used as a metaphor for falling hazards. The employer or contact person of each construction company is stimulated to involve all their workers in the selection, use and monitoring of safety measures to reduce falling hazards when working with rolling scaffolds, ladders and stairs.

### Control condition

In the control condition, no guidance strategies will take place, with the exception of a general announcement of inspection in construction companies.

### Outcome measure

Safety violations are the primary outcome measure and are defined as safety violations during the installation and use of equipment for working from heights. The labor inspectorate will check safety violations concerning equipment of rolling scaffolds, ladders and stairs on worksites of painters during a three-week period. The safety violations consist of 0 to 30 safety hazards (see below list). In addition, workers will be asked to specify the reasons for identified violations during the inspections.

### Safety violations

#### General

1. incomplete risk inventory and evaluation

2. no collective safety measures

3. equipment not suitable for type of work

4. no possibility to evacuate

5. extra falling hazard when stepping over

6. defective materials

7. defective construction

8. hazards for falling objects, electricity, heat

9. no annual technical examination

10. bad maintenance

#### Specific for rolling scaffolds

11. not safe to access working floor

12. working floor not completely closed

13. no side safeguarding working floor

14. no safeguarding when climbing floors

15. no (guarantee for) stability or strength testing

16. no (de)installation scheme or authorized

17. unstable on ground surface

18. inadequate angle braces

19. no prescribed stabilizer

20. no prescribed anchoring

21. no safeguarded wheels

22. flooring not adequate or secured

23. no competent worker for installation

24. no instruction for installation

25. climbing outside

26. transporting with persons on it

27. overloading

#### Specific for ladders and stairs

28. unstable during use

29. no horizontal steps

30. no safe grip with hand

### Process evaluation

The process evaluation of the two guidance strategies will be determined using indicators as defined by Linnan and Steckler [15], Murta et al. [16] and Bowen et al. [17]. The following indicators for implementation of the program will be evaluated [15,16]: reach, dose delivered, dose received. Satisfaction with the intervention (score 0–10), increase in perceived knowledge on safety measures (score 0–10) and perceived effectiveness on safety behavior (score 0–10) are used as indicators for acceptability concerning the interventions [17].

Reach is defined as the attendance rate of the construction companies at the intervention. Attendance rate is defined as the number of construction companies participating in this study relative to the number of eligible construction companies invited through the recruitment strategies. The attendance will be assessed by means of a logbook during the recruitment of the construction companies. Construction companies that do not participate will be asked to explain why.

Dose delivered refers to the proportion of the intended intervention that is actually delivered to the participating contact persons of the construction companies. For the face-to-face guidance strategy, the number of company visits and company reports including advice delivered by the safety consultants to the contact person of the construction companies will be assessed by means of a logbook filled in by the safety consultants and checked by Arbouw, who coordinate the company visits as applied by the safety consultants. For the direct mailing strategy, dose delivered will be assessed by means of the number of direct postal mails and emails to the contact person of the construction companies. The dose delivered is rated as sufficient when more than 90% of the companies receive the interventions (i.e. visit of the safety consultant and postal information).

Dose received refers to the proportion of activities in the intervention that are actually performed by the employer and workers of the construction companies. For both intervention strategies, dose received is assessed by three questions to the employer and two questions to the workers in a questionnaire after completion of the intervention period. For the face-to-face strategy, employers are asked if they have received a safety consultant (yes/no), have given feedback of advice to all workers (yes/no) and have taken preventive actions (yes/no; type of actions: education, training, buying safer equipment, supervision, appointment with suppliers, appointment with principal, other). The workers are asked if they have received information (yes/no) and if they have taken preventive actions (yes/no; type of actions: education, training, following equipment instruction, supervision with colleagues, appointment with suppliers, appointment with principal, other). For the direct mailing strategy, the employers are asked if they have read the postal and internet information (yes/no), if they have disseminated information to all workers (yes/no) and if they have undertaken preventive actions (yes/no; type of actions: education, training, buying safer equipment, supervision, appointment with suppliers, appointment with principal, other). The workers are asked if they have received information (yes/no) and if they have taken preventive actions (yes/no; type of actions: informing, training, following equipment instruction, supervision with colleagues, appointment with suppliers, appointment with principal, other).

Satisfaction is measured by asking the employers and workers how they rated their satisfaction with the intervention as a whole and its individual components, on a scale from 0 (not satisfied) to 10 (very satisfied).

Increased knowledge about working safely with rolling scaffolds, ladders and stairs as a result of the intervention is measured by asking the employers and workers to what extent their knowledge increased from (0–10; 0 = not more knowledge, 10 = much more knowledge). The rates are defined as not more knowledge (0), little (≥0 and <6), moderate (≥6 and <7.5) or much more knowledge (≥7.5).

Effect on working safely with rolling scaffolds, ladders and stairs as a result of the intervention is measured by asking the employers and workers to what extent the perceived effect on safety behavior is rated (0–10, 0 = no effect, 10 = large effect). The rates are defined as poor (<6), moderate (≥6 and <7.5) or good (≥7.5).

The process outcomes will be measured after the intervention period through questionnaires sent to the companies and their workers.

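### One yes/no question covers both post and website in the direct mail strategy, so dose received cannot show whether the internet component was used

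*Protocol article*

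**What the plan says.** The Process evaluation section of the protocol article defines the indicator: "Dose received refers to the proportion of activities in the intervention that are actually performed by the employer and workers". It also fixes the number of items for both strategies: "dose received is assessed by three questions to the employer and two questions to the workers".

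The first employer item differs by strategy. For direct mail, "the employers are asked if they have read the postal and internet information (yes/no". For face-to-face, "employers are asked if they have received a safety consultant (yes/no".

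The Direct mail guidance strategy section describes what is sent: "The paint pot contains a poster with URLs for the Internet approach". Those addresses lead to four types of material: brochures and poster, checklists, a video and a toolbox.

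The worker action lists differ in one label. Direct mail has "type of actions: informing, training, following equipment instruction, supervision with colleagues" and face-to-face has "type of actions: education, training, following equipment instruction, supervision with colleagues".

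**The concern.** Post and website are not interchangeable here. The poster is mainly a pointer, and most of the instruction lies behind the web addresses. Internet access is part of how the Abstract and Background define this strategy, and website development is a cost line in the Economic evaluation section.

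The Background says the process measures are there to give insight into implementation alongside the effect. Methodological considerations warns that the main comparison may lack power. If direct mail shows no effect, the reader will want to know whether the web material failed or was never opened. That bears on the roll-out considered in the Discussion, and a single merged answer cannot tell the two apart.

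**Working it through.** The plan states no figure for this item, so there is none to reproduce. The check is a reading of the items plus a short bound.

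**Step 1. What an answer can mean.** Take three employer states and two ways of reading the word 'and'.

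| Employer's true state | 'And' read strictly (both) | 'And' read loosely (either) |
|---|---|---|
| Read nothing | no | no |
| Read the post only | no | yes |
| Read the post and opened the site | yes | yes |

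The middle row moves between 'no' and 'yes' with the respondent's reading, and nothing in the answer shows which reading was used.

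**Step 2. How far the figure can move.** Let p be the share who read the post and w the share who opened the site. Assume that everyone who opened the site had also read the post. The strict reading returns w and the loose reading returns p, so the item is uncertain by p − w. That is zero if every reader opened the site and the whole of p if none did.

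The documents give neither share. With p = 80% and w = 25%, both assumed:
- strict reading: 25% 'yes'. The 75% 'no' mixes 100 − 80 = 20% who read nothing with 80 − 25 = 55% who read the post only;
- loose reading: 80% 'yes', mixing 25% who opened the site with 55% who did not;
- uncertain range: 80 − 25 = 55 percentage points.

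**Step 3. Whether another measure fills the gap.** In the Process evaluation section:
- dose delivered for direct mail counts postal mails and emails sent, and its criterion of more than 90% refers to postal information;
- the second employer item asks about passing information on, whatever its source;
- workers are asked whether they received information, with no channel named;
- satisfaction is rated for individual components, which may hint at use but does not measure it.

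None of these records whether the website was opened.

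**Step 4. The items side by side.** There are 3 employer + 2 worker = 5 items per strategy.

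| Item | Face-to-face | Direct mail | Parallel? |
|---|---|---|---|
| Employer 1 | received a consultant | read post and internet material | no |
| Employer 2 | passed advice to all workers | passed information to all workers | yes |
| Employer 3 | preventive actions | preventive actions, same list | yes |
| Worker 1 | received information | received information | yes |
| Worker 2 | preventive actions | preventive actions, one label differs | nearly |

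Four of five items are parallel or nearly so. Employer item 1 is not: it records receipt in one strategy and reading in the other, although the definition speaks of activities performed.

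**The case against.** The best defence is that the article describes the questionnaire in prose and does not reproduce it, so the form itself may hold separate sub-questions. That possibility remains. However, the text fixes three employer questions and words this one as a single yes/no, so a separate website question would depart from what is written. Component satisfaction ratings also give some indirect information, as noted above.

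A reader might infer more than the text supports, in three ways.

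- *That dose received as a whole cannot be compared between the strategies.* Four of the five items can be. Wording specific to each strategy is natural for an exposure question, and the Statistical analyses section plans t-tests only for satisfaction, insight and safe working behavior.
- *That the face-to-face item is worthless because visits are already logged.* The logbook is filled in by the consultants. An employer's own report is a reasonable cross-check, and employer items 2 and 3 cover activities performed. What stands is only that this item is not the counterpart of the direct mail one.
- *That offering 'informing' to direct mail workers inflates their preventive actions.* The option appears in a list of actions the worker takes, and a separate question already asks whether information was received. Face-to-face workers are informed in meetings as well, so a bias in one direction is not established. The difference may simply be loose wording.

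**Conclusion.** The point holds for one item. The first direct mail employer question gives an ambiguous figure, and the process evaluation as described cannot say whether the internet component was used. The extent is one of five dose-received items in a secondary, descriptive measure. The primary outcome, the randomization, the sample size and the planned tests are untouched.

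The conclusion assumes that the questionnaire follows the article's description and that no website count is kept elsewhere. The percentages above only illustrate the mechanism and do not predict this trial's results.

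**What to change.** In the Process evaluation section, replace the direct mail item with two yes/no items, one on reading the postal material and one on opening the website, and report them separately. Optionally, ask which of the four material types were used, and add site visit counts if they are available; the article does not mention any.

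State that employer item 1, and any composite that includes it, will not be compared between strategies, and that the other four items may be compared one by one. Use the same label in both worker lists in place of 'education' and 'informing'.

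The cost is one or two extra tick boxes and a slightly longer form. The questionnaire goes out after the intervention period, so the change is easy until then. Once it has been sent, use by channel is hard to recover and the ambiguity should be reported as a limitation.

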### Economic evaluation

A financial cost analysis for each intervention strategy will be made. The costs of the face-to-face strategy will be calculated by multiplying the number of company visits by the fixed cost per visit, plus travel costs, the coordination costs charged by Arbouw and the cost of information materials. The cost of the direct mailing strategy will be calculated by totaling the coordination costs charged by Arbouw, the costs of developing information materials and the website, and the costs of direct mailing.

### Sample size

The sample size is based on detecting an absolute difference in safety violations of 25% between the face-to-face guidance strategy and the control condition, and 15% between the direct mail strategy and the control condition. Data from previous inspection projects on equipment for working from heights revealed that in 84% of the cases safety violations were ascertained. We have decided that a 15-25% absolute reduction in ascertained safety violations concerning equipment for working from heights is a realistic and relevant difference.

Based on a power calculation using the nQuery Advisor® Version 7.0, 64 construction locations involved in painting and maintenance per group must be included to achieve a difference of 15% -25% (from 84% to 69% and 59% respectively) with an alpha of 0.05 (two-tailed) and a power of (1-beta) = 0.80. Based on previous inspections on rolling scaffolds, stairs and ladders, the assumption is made that at least half of the construction sites in the 27 large Dutch cities during May 2014 visited by the labor inspectorate are involved in painting and maintenance. Since the policy of the labor inspectorate is not to make a distinction between painting and non-painting companies, this results in a target for the inspections of 128 work sites per group.

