**Methods/Design:**

This study is a block randomized intervention trial in 27 cities to establish the effects of the face-to-face guidance strategy (N = 9), a direct mailing strategy (N = 9) and a control condition of no guidance (N = 9) on safety violations to record by labor inspectors after three months. A process evaluation for both strategies will be performed to determine program implementation (reach, dose delivered and dose received), satisfaction, knowledge and perceived safety behavior. A cost analysis will be performed to establish the financial costs for both strategies. The present study is in accordance with the CONSORT statement.

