### Statistical analyses

The primary outcome measures, i.e. ascertained safety violations, will be presented for the two guidance strategies and the control condition using descriptive statistics. The number of safety violations concerning the installing and use of equipment for working from heights at worksites of painting and maintenance companies ascertained by the Dutch labor inspectorate in the included 27 cities during three weeks in May 2014 will be retrieved by the primary researcher (HM) from the database of the Dutch labor inspectorate. Differences in the mean number of safety violations will be tested using an analysis of variance.

The three process measurements (i.e. satisfaction, insight and safe working behavior) of both intervention strategies are post-tested and converted into continuous variables on a scale of 0–100. The differences between both interventions are examined using independent t-tests.

The analysis is performed on an intention-to-treat basis. IBM SPSS 19.0 will be used for the statistical tests. Statistical significance is defined as p < 0.05 for all outcome measures.

The costs calculation for each intervention strategy will be analyzed descriptively.

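### The sample size is built on the share of sites with any violation, but the planned primary test compares the mean number of violations, so the stated 80% power does not belong to that test.

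*Protocol article*

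**What the plan says.** All references are to the protocol article.

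- **Sample size.** The baseline is a percentage: "Data from previous inspection projects on equipment for working from heights revealed that in 84% of the cases safety violations were ascertained". The targets are percentages too, "from 84% to 69% and 59% respectively", and a fall of 15 to 25 points is called realistic and relevant. The requirement is that "64 construction locations involved in painting and maintenance per group must be included", "with an alpha of 0.05 (two-tailed) and a power of (1-beta) = 0.80". About half of inspected sites are expected to be painting and maintenance sites, so "this results in a target for the inspections of 128 work sites per group".
- **Outcome measure.** The primary outcome is safety violations, described as a count: "The safety violations consist of 0 to 30 safety hazards".
- **Statistical analyses.** One test is named for the primary outcome: "Differences in the mean number of safety violations will be tested using an analysis of variance".

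The article gives no mean, standard deviation or relevant difference for the count, and plans no test of the share of sites with a violation.

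**The concern.** The sizing treats each site as violating or not. The analysis treats each site as a number between 0 and 30. These are different outcomes, and the power of a test on one does not carry over to the other unless the distribution of the count is known.

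They can also move apart. Suppose every violating site goes from four violations to two: the mean halves while 84% of sites still violate. Conversely, the share could fall by 15 points while a few sites with many rolling-scaffold violations hold the mean up (17 of the 30 listed items are specific to rolling scaffolds). Both cases are hypothetical, but they show that a significant difference in means need not be the 15 to 25 point reduction that the article calls relevant, and that a non-significant one need not rule that reduction out.

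At stake is how the primary result is read. A null result would be reported as coming from a trial with 80% power, although that figure was never worked out for the test performed.

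**Working it through.** **Inputs from the article.** Shares 0.84, 0.69 and 0.59; n = 64 per group; three groups; two-sided alpha 0.05; power 0.80 (Sample size). Count from 0 to 30 (Outcome measure). Analysis of variance on means (Statistical analyses). Sites are taken as independent throughout, as the sizing appears to do.

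**Step 1: reproduce 64.** For a three-group chi-square test with 2 degrees of freedom, the noncentrality is λ = n × Σ(pᵢ − p̄)² / [p̄(1 − p̄)].

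- p̄ = (0.84 + 0.69 + 0.59)/3 = 0.7067
- Σ(pᵢ − p̄)² = 0.01778 + 0.00028 + 0.01361 = 0.03167
- p̄(1 − p̄) = 0.7067 × 0.2933 = 0.2073
- λ per site per group = 0.03167/0.2073 = 0.1528
- n = 63: λ = 9.62, power 0.7995
- n = 64: λ = 9.78, power 0.806

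So 64 is the smallest group size reaching 80%. Pairwise tests of proportions do not give it: 84% against 59% needs 50 per group (58 with continuity correction), and 84% against 69% needs 125 (138). The sizing is therefore arithmetically right, for a three-group test of proportions.

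**Step 2: what the planned test would need.** For a three-group analysis of variance with 64 per group (2 and 189 degrees of freedom), 80% power needs λ = 9.79, so Cohen's f = √(9.79/192) = 0.226. With the three means spaced as the percentages are, the largest standardised difference is about 0.55. Without a standard deviation for the count, the article does not let a reader say whether 15 to 25 points corresponds to that.

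**Step 3: does 80% carry over?** Here λ = 64 × Σ(mᵢ − m̄)² / mean variance. The count distributions below are assumptions; each keeps the shares at 84%, 69% and 59%.

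*(a) Some sites become clean and the count at violating sites is unchanged.* With mean c and standard deviation s among violating sites, mᵢ = pᵢc and varianceᵢ = pᵢ(s² + c²) − mᵢ². Example with c = 3, s = 2: means 2.52, 2.07 and 1.77; variances 4.57, 4.69 and 4.54 (average 4.60); Σ(mᵢ − m̄)² = 0.285; λ = 64 × 0.285/4.60 = 3.97; power 0.41.

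*(b) The whole distribution shifts.* For a Poisson count with zero fractions 16%, 31% and 41%, mᵢ = −ln(1 − pᵢ) = 1.83, 1.17 and 0.89; Σ(mᵢ − m̄)² = 0.467; average variance 1.298; λ = 64 × 0.467/1.298 = 23.0; power 0.99.

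| Assumed count | Power of the analysis of variance, 64 per group |
|---|---|
| Every violating site has exactly 1 violation | 0.82 |
| (a) mean 2, SD 1 among violating sites | 0.53 |
| (a) mean 3, SD 2 | 0.41 |
| (a) mean 4, SD 3 | 0.36 |
| (a) mean 3, SD 3 | 0.25 |
| (b) Poisson shift | 0.99 |

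These are illustrations, not bounds: a more dispersed case of type (a), mean 3 and SD 4, gives 0.17.

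**Step 4: pairwise power on the share.** The Sample size section words its target as two contrasts with control. At 64 independent sites per group, a two-sided 0.05 test of two proportions has power 0.52 for 84% against 69% and 0.89 for 84% against 59%.

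**The case against.** The best defence is that the article is clear about its primary analysis. Only one test is named, and the count also fits the Background and the Methodological considerations, which speak of lowering the number of violations. On that view the percentages are a rough planning device, and the count may be the more sensitive outcome, so the trial could have more than 80% power.

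Much of this stands, and it rules out three stronger readings.

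- A reader might infer that the primary result could be picked after the data are seen. The text does not support that: no test of the share is planned, so there are not two competing primary analyses.
- A reader might infer that the trial is underpowered for its planned test. The documents do not show this: a shift of the whole distribution gives power near 0.99.
- A reader might infer that the 80% can have no bearing at all on the analysis of variance. That goes too far: if sites score only 0 or 1, its power is 0.82.

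What the defence does not remove is that the article attaches a power figure and a relevant difference to one outcome and then tests another. This is not detail left to a fuller document. Both statements are in the article, and further detail on the analysis would not turn a sizing on proportions into one on means.

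**Conclusion.** The point holds as a mismatch between sizing and analysis. The figure of 64 per group is correct for a three-group test of 84%, 69% and 59%, and neither its 80% power nor the 15 to 25 point target applies to the planned analysis of variance on the mean count. The actual power of that test rests on a count distribution that the article does not state: about 0.25 to 0.99 across the main cases worked, with independent sites, so the direction of the error is unknown. Randomisation by city is a separate matter; none of these figures allows for it.

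This should be fixed, but it does not invalidate the design. The same inspection data serve either outcome.

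**What to change.** Either of two repairs brings sizing and analysis together.

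**(a) Make the share primary.** Define the primary outcome as the share of inspected painting and maintenance sites with at least one ascertained violation, test it across the three groups as it was sized, and report the count as secondary. State alongside that at 64 independent sites per group, pairwise power against control is only about 0.52 for direct mail and 0.89 for face-to-face, before any allowance for randomisation by city. Cost: changes of wording to the outcome and analysis sections, with no new data. The count, which may be more sensitive, becomes secondary, and the direct mail contrast is openly weak.

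**(b) Keep the count primary.** Withdraw the claim of 80% power for this test and replace it with a statement based on a mean, standard deviation and relevant difference in the number of violations, for example from the previous inspection data. Cost: those figures must be obtained and a relevant difference in the count justified. The required number of sites may then prove larger or smaller than 64 per group.

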### Hypothesis

We hypothesize that both guidance strategies will reduce safety violations with rolling scaffolds, ladders and stairs compared to the control condition of a general announcement of inspection in construction companies. In addition, the face-to-face strategy is thought to be superior to the direct mail strategy. This is expected to be due to a higher impact of personalized feedback in the face-to-face guidance strategy on executing safety measures within the construction companies compared with awareness-raising in the direct mail strategy. The financial costs are expected to be higher in the face-to-face guidance strategy, especially due to hiring safety consultants and their coordinator for work site visits.

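### The 64 sites per group give about 80% power for an overall three-group test, but only about 52% for the stated 15-point direct-mail difference from control

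*Protocol article*

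**What the plan says.** The Sample size section of the protocol article bases the calculation on two comparisons with control. The first is "detecting an absolute difference in safety violations of 25% between the face-to-face guidance strategy and the control condition". The second, smaller target is a difference of "15% between the direct mail strategy and the control condition". The control rate comes from earlier inspection projects, where "in 84% of the cases safety violations were ascertained". The target rates are given as "from 84% to 69% and 59% respectively". The conclusion is that "64 construction locations involved in painting and maintenance per group must be included to achieve a difference of 15% -25" percentage points, and the calculation is said to have been made "with an alpha of 0.05 (two-tailed) and a power of (1-beta) = 0.80". The section then doubles 64 to 128 inspected work sites per group, because at least half of the inspected sites are assumed to be painting and maintenance sites.

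The Hypothesis section expects both strategies to beat control and adds that "the face-to-face strategy is thought to be superior to the direct mail strategy". The Statistical analyses section plans an analysis of variance on the mean number of violations at painting and maintenance worksites. The Sample size section does not say that 64 belongs to an overall three-group test.

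**The concern.** One sample size is attached to two differences of unequal size, at a single stated power. Read plainly, the section promises 80% power for the 15-point difference as well as for the 25-point one. The smaller difference must need more sites than the larger, so 64 cannot be the 80% figure for both.

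The smaller difference belongs to direct mail versus control, one of the two comparisons in the study objective. The Discussion ties wider implementation to whether the strategies prove effective. If readers take the design to have 80% power for direct mail when it has about half, they will give a non-significant direct-mail result more weight than it can bear.

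**Working it through.** **Inputs (Sample size section).** Control 84%, direct mail 69%, face-to-face 59%; two-sided alpha 0.05 (z = 1.960); power 0.80 (z = 0.842); equal groups. Sites are treated as independent, and the outcome is whether a site has a violation.

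**1. Where 64 comes from.** Overall chi-square test of three proportions, 2 df, with noncentrality λ = n × Σ(p − p̄)² / [p̄(1 − p̄)].
- p̄ = (0.84 + 0.69 + 0.59)/3 = 0.7067
- Σ(p − p̄)² = 0.03167; p̄(1 − p̄) = 0.2073; ratio = 0.15277
- n = 63: λ = 9.62, power 0.7995
- n = 64: λ = 9.78, power 0.8061

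The smallest n that reaches 0.80 is 64, so the plan's figure is reproduced exactly.

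**2. Pairwise versions do not give 64.** The pooled formula is n = [1.960 × √(2p̄(1 − p̄)) + 0.842 × √(p1(1 − p1) + p2(1 − p2))]² / (p1 − p2)², with p̄ now the mean of the two rates. Entries are sites per group.

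| Variant | 84% vs 59% | 84% vs 69% |
|---|---|---|
| Two-sided, pooled | 50 | 125 |
| Two-sided, continuity-corrected | 58 | 138 |
| One-sided | 40 | 98 |
| One-sided, continuity-corrected | 47 | 111 |
| Unpooled | 48 | 122 |
| Arcsine | 49 | 123 |
| Alpha 0.025 | 61 | 151 |
| Alpha 0.0167 | 67 | 166 |

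None falls within 2 of 64.

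**3. Pairwise power at 64 per group.** Power = Φ{[|p1 − p2|√n − 1.960 × √(2p̄(1 − p̄))] / √(p1(1 − p1) + p2(1 − p2))}.
- Direct mail vs control: (0.15 × 8 − 1.960 × 0.5996)/0.5902 = 0.042, power 51.7% (exact enumeration of the Pearson test: 52.2%)
- Face-to-face vs control: (0.25 × 8 − 1.960 × 0.6384)/0.6134 = 1.221, power 88.9% (exact: 89.6%)

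**4. Smallest detectable reduction at 64.** From 84%, a fall to 63% (21 points) has 77.4% power and a fall to 62% (22 points) has 80.8%. The pairwise detectable reduction is therefore about 22 points.

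**5. Effect of randomising cities.** There are nine cities per arm, so 64/9 ≈ 7.1 sites per city. The article gives no intracluster correlation (ICC); 0.01 to 0.10 is assumed here. Design effect = 1 + (7.11 − 1) × ICC.
- ICC 0.01: design effect 1.06, effective n = 64/1.06 ≈ 60, direct-mail power about 49%
- ICC 0.10: design effect 1.61, effective n = 64/1.61 ≈ 40, direct-mail power about 35%

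**6. Side remark.** Face-to-face vs direct mail at 69% vs 59%: (0.10 × 8 − 1.960 × 0.6788)/0.6751 = −0.786, power about 22%.

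**The case against.** The best defence is that 64 is correct for an overall comparison of three groups, and that the only test named for the primary outcome, an analysis of variance, is also an overall test. The first part stands: nothing has been miscalculated. It does not rescue the text, because the section names two separate differences from control as its basis and never mentions an overall test. An overall test also cannot show which strategy works.

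A second defence is that 128 sites per group will be inspected; with 128 analysed sites, direct-mail power would be about 81%. But the doubling only allows for non-painting sites, and the analysis is confined to painting and maintenance worksites. The planned analysed number is 64. Because at least half are assumed to be painting sites, 64 is the low end of the planning assumption, so the analysed number and the power could turn out somewhat higher.

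A third is that the Methodological considerations section already warns of a possible lack of power. It gives a different reason, too few participating companies at the inspected sites, so it does not answer this point.

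Two stronger readings are tempting but unsupported. A reader might infer that 80% power is also claimed for face-to-face versus direct mail. It is not: superiority is an expectation with no stated power, so the 22% contradicts nothing. A reader might also infer that a null direct-mail result will be reported as no effect. Nothing in the article says so.

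**Conclusion.** The concern holds as a wrong description of what 64 achieves, not as an arithmetic error. For direct mail versus control, a contrast the section names, power is about 52% rather than 80%, a shortfall of about 28 points; about 125 sites per group would be needed (138 with continuity correction). Face-to-face versus control is adequately powered on the plan's own inputs, at about 89%.

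These results rest on the stated rates, 64 analysed sites per group, independent sites, no multiplicity adjustment, and a comparison of proportions. At 64 sites they are upper limits, because any positive correlation within cities lowers them. They do not carry over directly to the planned analysis of variance on mean counts.

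**What to change.** Keep 64 painting sites (128 inspections) per group and reword the Sample size section to state that:
- for the proportion of sites with a violation, and assuming independent sites, 80% is the power of the overall three-group test;
- on the same assumptions, power against control is about 89% for face-to-face and about 52% for direct mail, and the smallest reduction from 84% detectable pairwise with 80% power is about 22 points;
- these are upper limits at 64 analysed sites because cities are randomised, nine per arm; with an assumed ICC of 0.01 to 0.10 and about 7 sites per city, direct-mail power is about 49% to 35%;
- the figures do not apply directly to the analysis of variance on the mean number of violations.

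Add to Statistical analyses that each pairwise contrast will be reported with its 95% CI, and that a non-significant direct-mail contrast will not be interpreted as no effect.

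The cost is a paragraph of wording and a less favourable stated power. No extra sites or inspections are needed.
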